### 3.8. Statistical Analysis Methods

The data obtained will be summarized using summary statistics (mean, standard deviation, median, and interquartile range) or frequencies and percentages, both overall and stratified by dose. For each dose, estimates of the positive diagnostic rate, sensitivity, specificity, and 95% confidence intervals will be calculated based on the Wilson score method. In addition, the mean and 95% confidence intervals of the numerical values of wavelength intensity in the peak range of the ICG fluorescence wavelengths will be calculated and compared between doses using an analysis of variance. Subgroups, such as expanded vs. collapsed lungs and non-tumor vs. tumor areas, will also be examined. Adverse events will be presented as the number of occurrences per dose.

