## 2. Experimental Design and Detailed Procedure

### Study Design

This is a single-center, open, dose-comparison control, interventional clinical trial.

The trial has been registered in the jRCT Clinical Trials Registry under the code jRCTs011230037 (https://jrct.niph.go.jp/en-latest-detail/jRCTs011230037) (accessed on 28 March 2024).

The detailed procedure is described in Figure 1.

The data obtained will be used for analysis until 1 August 2026. Subsequently, the data will be stored and may be used for future studies.
(1)Dissolve indocyanine green (ICG) (Diagnogreen^®^, Daiichi-Sankyo, Tokyo, Japan) in 5 mL to 10 mL of the attached injection solution, dilute it with 200 mL of saline solution to make a total volume of approximately 205–250 mL, and inject it intravenously the day before surgery (approximately 24 h (window of 22 to 26 h) before the surgery) over approximately 1–2 h. The dose should be in the range of 0.5 mg/kg to 5.0 mg/kg. The initial dose should be 0.5 mg/kg. If the positive diagnosis rate is low, the dosage should be increased at 1.0 mg/kg intervals to a maximum of 5.0 mg/kg to determine the optimal dosage for detecting tumors.(2)The probe of the fluorescence spectroscopy system is used in the thoracic cavity, and the ICG is excited by the excitation light source when the probe is applied to the lung tumor to observe whether a fluorescence wavelength is detected. Measure the distance from the surface of the lung to the probe, and the distance from the surface of the lung to the tumor.(3)Pulmonary lobectomy and more extensive surgical approaches are performed as usual in our department. The probe of the fluorescence spectroscopy system is applied to the resected lung removed from the thoracic cavity to generate ICG fluorescence using an excitation light source to determine if the fluorescence wavelength is detected.(4)Postoperative observation of patient for 1 to 2 weeks.

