### 3.3. Allocation Method

The initial ICG dose will be 0.5 mg/kg. Thereafter, the dose will be increased to 1.0 mg/kg, 2.0 mg/kg, and so on, at 1.0 mg/kg intervals to a maximum of 5.0 mg/kg. In this study, the lowest dose of ICG used for blood flow evaluations during the segmentectomy of the lungs and liver was 0.5 mg/kg. Additionally, for the purpose of a safety evaluation, a minimum dose of 0.5 mg/kg was established. Ten patients will be allocated this in order from the lowest dose, resulting in a total sample size of 60 patients.

The sensitivity and specificity of tumor detection at each dose will be calculated using the following formulae.

Sensititvity = number of cases in which tumors were identified by the fluorescence spectroscopy system/total number of cases in which pathology resulted in a diagnosis of malignancy.

Specificity = number of cases in which no tumor was identified by the fluorescence spectroscopy system/total number of cases in which pathology showed a benign tumor.

The most suitable dose for tumor detection will be determined by taking into consideration both accuracy and dosage. While the maximum dose is 5.0 mg/kg, if the positive detection rate becomes 0.9 or higher at a certain dose, and improvement in the positive detection rate cannot be expected further by increasing the dose thereafter, the dosage should not be increased. 

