### 3.6. Target Number of Patients

A maximum of 60 patients will be enrolled, including 10 patients per dosage level.

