## 4. Expected Results and Discussion

Our research is dedicated to assessing the capabilities of an advanced ICG fluorescence spectroscopy system to enhance tumor localization during thoracoscopic surgery. Our prior investigations into this state-of-the-art system have shown its proficiency in identifying tumors located deeper than the lung surface—regions that conventional ICG cameras struggle to reveal [15]. A particular challenge has been detecting lung tumors smaller than 5 mm and situated more than 20 mm beneath the surface, which are often not visible with standard ICG cameras or to the naked eye. Based on previous studies, to achieve this objective, we intravenously administer ICG and image it at a later time (24 h after delivery, during the second window) [12]. The feasibility of NIR imaging in the second window is due to the dye’s accumulation in tissues with abnormally leaky capillaries and/or increased pressure gradients through the EPR effect.

The novel spectral system we have developed for our current study distinguishes itself by detecting NIR light wavelengths through specialized instruments, potentially identifying lesions undetectable when using traditional ICG cameras [15]. Our preliminary results have shown that while conventional ICG cameras falter in identifying pseudo-tumors concealed by more than 10 mm of tissue or tissue substitute, our spectral analysis device can discern spectra obscured by even thicker layers. These findings highlight the crucial roles of both the distance between the tumor and the probe and the density of the tissue between them in the detection of ICG wavelengths.

We are poised to launch a clinical trial to appraise the system’s utility in surgical navigation, focusing particularly on the fluorescence spectrum of lung cancer and metastatic lung tumors. This study will encompass patients slated for lung resection due to these conditions, employing the ICG system to intraoperatively examine the fluorescence spectrum of their tumors and to further analyze the excised tissue postoperatively. The surgical procedures will conform to standard lung resection protocols.

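### The only stated between-dose test of fluorescence intensity ignores dose order and gives the recorded distances no role: valid, but inefficient

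*Protocol article*

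**What the plan says.** Section 3.8 (Statistical Analysis Methods) fixes one between-dose method for intensity: means with 95% confidence intervals are "calculated and compared between doses using an analysis of variance". It names no trend test, contrast or covariate. It continues: "Subgroups, such as expanded vs. collapsed lungs and non-tumor vs. tumor areas, will also be examined", without naming a method.

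The doses are ordered and quantitative. After 0.5 mg/kg, "the dose will be increased to 1.0 mg/kg, 2.0 mg/kg, and so on, at 1.0 mg/kg intervals to a maximum of 5.0 mg/kg" (section 3.3), and "A maximum of 60 patients will be enrolled, including 10 patients per dosage level" (section 3.6). Escalation may end early: once the detection rate reaches 0.9 and "improvement in the positive detection rate cannot be expected further by increasing the dose thereafter, the dosage should not be increased" (section 3.3).

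The procedure in section 2 includes the instruction "Measure the distance from the surface of the lung to the probe, and the distance from the surface of the lung to the tumor". Section 4 reports that preliminary results highlight "the crucial roles of both the distance between the tumor and the probe and the density of the tissue between them" in detecting ICG wavelengths.

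Tumor intensity, and collapsed against expanded lung, are secondary endpoints (section 3.4). Section 3.13 refers to a separate statistical analysis plan, which is not shown.

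**The concern.** The trial aims to find a suitable dose, and its doses form a ladder. An omnibus analysis of variance spends up to five degrees of freedom asking whether any doses differ; relabelling the doses in any order would leave its result unchanged. With 10 patients per dose, that is a costly way to look for a response expected to rise or level off, which is what the escalation rule presumes.

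The stated comparison also leaves unused two measurements that the article collects and whose importance it stresses. If they explain part of the patient-to-patient variation in signal, an unadjusted comparison carries that variation as noise.

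Finally, lung state and tissue site are called subgroups. That term normally means different patients, whereas the same lung can be collapsed and expanded, and the same patient can supply tumor and non-tumor tissue. At stake is the power and clarity of a secondary analysis that supports the dose choice.

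**Working it through.** **The plan's own figure.** The article gives no power, SD or effect size for intensity. Its 10 per dose comes from the primary rate (section 3.7). With a true rate of 0.9 and n = 10, the 95% Wilson interval has full width at most 0.4 only for 9 or 10 correct results (widths 0.386 and 0.278). The probability is 10 × 0.9⁹ × 0.1 + 0.9¹⁰ = 0.387 + 0.349 = 0.736. The stated 70% is therefore met if 0.4 is read as full width. I take 10 per dose as given.

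**Inputs.** From the article: doses 0.5, 1, 2, 3, 4, 5 mg/kg and m = 10 per dose, so 60 patients and 54 residual degrees of freedom. Assumed: two-sided 5% level, residual SD 1, and a rise of 1 SD from lowest to highest dose, either linear in dose or linear in log dose.

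**Formulas.** With dose means μᵢ:
- Omnibus test: noncentrality λ = m Σ(μᵢ − μ̄)²/σ², on 5 and 54 df, critical F 2.386.
- Trend: λ₁ = m (Σcᵢμᵢ)²/(σ² Σcᵢ²), where cᵢ is centred log dose, on 1 and 54 df, critical F 4.020.

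Power is the upper tail of the noncentral F distribution.

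**Six doses, no adjustment.**
- Linear shape (0, 0.111, 0.333, 0.556, 0.778, 1): Σ(μᵢ − μ̄)² = 0.751, so λ = 7.51 and power is 49%. For the log-dose trend, λ₁ = 6.87 and power is 73%.
- Log shape (0, 0.301, 0.602, 0.778, 0.903, 1): the sum is 0.733, so λ = 7.33 and power is 48%. For the log-dose trend, λ₁ = 7.33 and power is 76%.

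A trend on untransformed dose gives 77% and 72% for the two shapes, so the choice of scale matters by about 4 percentage points.

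**Adjustment for distance.** Suppose the distances explain 30% of the within-dose variance and are unrelated to dose. Then σ² = 0.7, and λ becomes 7.51/0.7 = 10.73 or 7.33/0.7 = 10.47. Omnibus power is 65–66%. For the trend, λ₁ is 6.87/0.7 = 9.81 or 10.47, and power is 87–89%. Spending two further degrees of freedom on the covariates does not move these rounded ranges.

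**Other effect sizes (linear rise, trend on untransformed dose).** A rise of 0.8 SD gives 32% against 58%; 1.2 SD gives 67% against 90%.

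**Early end of escalation.** With three doses (0.5, 1, 2), a linear 1-SD rise across them and 27 residual df, λ = 5.19 and omnibus power is 47%. Trend power is 58% on log dose and 59% on dose.

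**Non-monotone response.** With means 0, 0.5, 1, 1, 0.6, 0.2 SD, λ = 10 × 0.835 = 8.35 and omnibus power is 54%. The log-dose trend has λ₁ = 1.24 and power 19%; the linear trend has λ₁ = 0.09 and power 6%.

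**Lung state and tissue site.** If both measurements come from one patient with correlation ρ, an unpaired standard error exceeds the paired one by the factor 1/√(1 − ρ): 1.20, 1.41 and 1.83 at assumed ρ of 0.3, 0.5 and 0.7. This applies only if an unpaired analysis were run, and section 3.8 names none.

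**The case against.** The analysis of variance is a legitimate test. Its type I error is unaffected, it does not rule out dose contrasts, and it does better if signal falls at high dose. Covariates and paired or mixed models are ordinary content for the statistical analysis plan, which section 3.13 says exists. Intensity is secondary: escalation follows the positive detection rate, and the dose choice rests on accuracy and dosage (section 3.3). All of this stands and limits the point. It does not remove it, because the article has already named a between-dose method, and a more efficient one uses variables it already records.

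Three stronger readings are tempting and are not supported.

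- **Paired data are analysed with the wrong standard error.** Section 3.8 says only that these comparisons will be examined; no test or standard error is given. Pairing itself is implied and not stated: section 2 does not say that each patient is measured in both lung states or at a non-tumor site. If an unpaired test were used on positively correlated pairs, the intervals would be too wide, which is a conservative fault.
- **Depth confounds the dose comparison.** Two groups of 10 differ in mean depth with a standard error of √(2/10) = 0.45 SD, but this is chance variation, already counted in the residual term of the analysis of variance. It would arise equally under randomisation. Allocation in dose order could admit drift over time, but nothing in the article shows drift in depth, and Table 1 limits depth to 2 cm at every dose. What is shown is lost precision.
- **Intensity is the trial's leading dose evidence.** The article gives it no such role.

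**Conclusion.** The point holds as one of efficiency. The stated intensity comparison is valid, but it ignores dose order and assigns no role to distances that the article records. Under an assumed monotone 1-SD rise over all six doses, a log-dose trend gains about 24 to 28 percentage points of power. If escalation stops after three doses, the gain is about 11 to 12 points. Adjustment for distance adds to either test in proportion to the variance that distance explains; 30% is an assumption.

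Every power figure is illustrative, because the article gives no SD, effect size, explained variance or correlation for intensity. The advantage reverses for a clearly non-monotone response, so the trend should be added and should not replace the existing test. The wording on lung state and tissue site needs clarifying but is not a demonstrated error. The change is worth making before intensity data are analysed; the primary endpoint does not depend on it.

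**What to change.** In section 3.8 or the statistical analysis plan:

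1. For tumor intensity, add a one-degree-of-freedom dose-trend test, with the dose scale (for example log dose) fixed in advance and with probe-to-surface distance and tumor depth as covariates. Limit this model to tumor measurements, since tumor depth has no evident meaning at a non-tumor site.
2. Keep the omnibus analysis of variance alongside it, to pick up a plateau followed by a fall or any other departure from a steady trend. State which of the two leads.
3. Where the same patient is measured in both lung states, or at both tumor and non-tumor sites, call these within-patient comparisons and report the paired differences with 95% confidence intervals. State how patients with only one measurement are handled.

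The cost is a few lines of text and a little analysis work. Dose and both distances are already recorded, and no patient, visit or procedure is added. The small downside is a second test on a secondary endpoint.

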### 3.9. Anticipated Benefits and Disadvantages (Burdens and Risks)

Anticipated Benefits: The use of ICG and fluorescence spectroscopy during surgery may uncover lesions, such as pleural seeding, not identified in preoperative assessments. These discoveries could inform real-time adjustments to surgical techniques or treatment plans, potentially avoiding unnecessary procedures and optimizing patient care through integrated therapies, including chemotherapy. Furthermore, the insights gained could advance the development of comprehensive, multidisciplinary treatment approaches.

Anticipated Disadvantages (Burdens and Risks): Adverse reactions, as detailed in the ICG package insert, may include shock, anaphylaxis, and hypersensitivity reactions (e.g., nausea, urticaria, fever), with a frequency of less than 0.1%. ICG administration intravenously may also cause discomfort at the injection site.

While the Lumifinder system is approved for laparoscopic use, it is not specifically indicated for thoracoscopic procedures. However, its intraperitoneal application suggests a low risk of adverse events during thoracoscopic use. The application of Lumifinder’s probe to lung tumors may extend surgical times by up to 15 min, although this is not expected to delay the overall duration of surgery or affect patient recovery. Participation in this study will not increase the volume or frequency of blood tests.

Comprehensive Evaluation: This study does not promise direct benefits to its participants. The main concerns are discomfort from the IV insertion and the rare side effects of ICG. These factors are unlikely to impact overall treatment outcomes. To mitigate risks, individuals with allergies to ICG, iodine, or contrast agents will be excluded from participation.

### 3.10. The Handling of Adverse Events

Treatment of Research Subjects in the Event of an Adverse Event: An adverse event is defined as any undesirable or unintended injury, illness, or symptom (including abnormal laboratory findings) that occurs in a research subject, irrespective of its causal relationship with the research activities. Upon observing an adverse event, the responsible researcher must promptly initiate the appropriate actions and treatment. Details such as the name of the adverse event, date of onset, severity (mild, moderate, severe), outcome, and its relationship to the study (related or unrelated), among other information, must be meticulously recorded. In cases where the study intervention is halted or a specific treatment for the adverse event is required, the research subject will be duly informed.

Reporting of Serious Adverse Events: Serious adverse events are characterized as 1. Resulting in death; 2. Being life-threatening; 3. Necessitating or prolonging hospitalization; 4. Leading to persistent or significant disability or dysfunction; or 5. Resulting in congenital anomalies or birth defects in offspring.

Upon the identification of a serious adverse event, the principal investigator (or an authorized delegate) is obliged to undertake necessary actions, including informing the affected research subjects, and to report the event expeditiously to the overseeing principal investigator. This lead investigator is then responsible for promptly notifying the administrative heads of the medical institution, taking suitable measures, and ensuring that all research personnel and relevant parties are informed about the incident.

The Reporting of Significant Adverse Events:

Significant adverse events include, but are not limited to, conditions like eczema, nausea, vomiting, etc., associated with the administration of ICG and any adverse event resulting in the discontinuation of the study intervention.

Investigators must report incidents qualifying as significant adverse events with the same urgency as serious adverse events.

Documentation of Other Adverse Events: all other adverse events, regardless of severity, must be accurately documented in the medical records by the principal investigator or a designated sub-investigator.

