### 3.12. Discontinuation of the Entire Study

The principal investigator may consider halting the entire study under any of the following conditions. In the event of such a discontinuation, the investigator is required to inform the Review Committee and the Minister of Health, Labour and Welfare, using the designated form, within 10 days. Additionally, the investigator must promptly notify the administrative head of the medical institution conducting the study and all participating research subjects, ensuring their safety through necessary examinations and interventions.

Conditions for Study Discontinuation: 1. Discovery of information that challenges the ethical integrity or scientific validity of the study or impacts its continuation. 2. Acquisition of facts or information that may compromise the proper conduct or credibility of the research findings. 3. Determination that the research risks outweigh the expected benefits, or the receipt of information suggesting that the research will not yield meaningful results. 4. The receipt of significant data concerning the quality, safety, or effectiveness of the research equipment that necessitates the termination of the study.

Furthermore, if there is a grave breach of the Clinical Research Act, this research protocol, or the relevant agreements by the medical institution or its staff, or if the proper conduct of the research becomes untenable, the principal investigator may request that the institution ceases or pauses the research. In cases where the study is halted or suspended due to reasons originating within the implementing institution, such as recommendations or directives from the review committee to stop the research or advisories from the Review Committee to alter the research plan in ways that are impractical to implement, the investigator will swiftly inform all participating research subjects and take the necessary steps to ensure their safety.

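### One related/unrelated flag to the study, with adverse events counted only per ICG dose, does not separate ICG, probe and operation from surgery onward

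*Protocol article*

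**What the plan says.** Section 2 (Study Design) adds two exposures to usual surgery. ICG is infused 22 to 26 h before the operation, at a dose that may rise from 0.5 to 5.0 mg/kg. The spectroscopy probe is then used inside the thoracic cavity. Section 3.9 says of the device: "While the Lumifinder system is approved for laparoscopic use, it is not specifically indicated for thoracoscopic procedures". It infers low thoracic risk from the device's intraperitoneal use.

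For each adverse event, section 3.10 asks for the name, onset date, severity, outcome and "its relationship to the study (related or unrelated"), among other information. It defines a class of significant events: "Significant adverse events include, but are not limited to, conditions like eczema, nausea, vomiting, etc., associated with the administration of ICG". The same definition has a second limb that is not tied to a product: "and any adverse event resulting in the discontinuation of the study intervention". Events in this class are expedited: "Investigators must report incidents qualifying as significant adverse events with the same urgency as serious adverse events". Serious events are reported whatever their cause. For the remainder, "all other adverse events, regardless of severity, must be accurately documented in the medical records".

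Section 3.8 states: "Adverse events will be presented as the number of occurrences per dose". Section 3.4 defines the safety endpoint as adverse events seen once the study drug has been given. Section 3.12 lists four conditions for halting the whole study. The first three are general. The fourth is "The receipt of significant data concerning the quality, safety, or effectiveness of the research equipment that necessitates the termination of the study".

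**The concern.** The trial changes two things at once, but the causality item has one target, the study. A related event could belong to the ICG dose or to the probe, and the item does not say which. The only stated presentation is by ICG dose, which is the right axis for a drug effect. For a probe used in the same way at every dose level, it splits the evidence into groups of ten.

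Two readings are at stake. A per-dose count is naturally read as information on ICG tolerability, yet it will also contain probe events and ordinary complications of lung resection. And the low-risk premise for using the probe in the chest has no summary of its own.

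The products named also differ between sections. The significant-event examples in 3.10 concern ICG. The one halting condition in 3.12 that names a product concerns the equipment, although ICG is the product being escalated.

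**Working it through.** The plan gives no figure for this point, so the check is mainly a comparison of sections, followed by arithmetic on what per-dose counts can show.

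**1. What can be attributed, by time of onset**
- Between infusion and surgery (about 22 to 26 h, section 2): the probe has not been used. Event name and onset date (section 3.10) exclude the probe and the operation.
- From surgery onward: ICG has been given, the probe has been in the chest and the lung has been resected. Event name helps for some events, but the single flag does not distinguish the three sources.

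**2. Where a probe event goes under section 3.10**
- Serious, including an event that prolongs hospitalization: expedited, whatever the product.
- Leads to discontinuation of the intervention: significant, expedited. This helps little for the probe, whose use adds at most 15 min (section 3.9) and may be over before harm appears.
- Non-serious, no discontinuation: expedited only if the investigator uses the open wording to class it as significant. Otherwise it is documented in the medical record.

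**3. Products named**
- 3.10, significant-event examples: ICG.
- 3.12, condition 4: equipment.
- 3.12, conditions 1 to 3: no product, so they can cover ICG harm.
- 3.4, safety endpoint: starts at the drug. Probe events fall inside it because the probe comes later, but they are not identified as such.

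**4. What counts per dose can show**
Inputs: 10 patients per level, up to six levels, at most 60 patients (sections 3.3 and 3.6).

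Weight of one event: 1/10 = 10 percentage points in a level; 1/60 = 1.7 points over all patients.

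Chance of at least one event, 1 − (1 − p)^n. The value 0.1% is the ceiling section 3.9 gives for ICG hypersensitivity reactions; the other rates are assumed.

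| True rate p | n = 10 | n = 60 |
|---|---|---|
| 0.1% | 1.0% | 5.8% |
| 1% | 9.6% | 45.3% |
| 5% | 40.1% | 95.4% |
| 10% | 65.1% | 99.8% |

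Exact two-sided 95% upper bound after zero events, 1 − 0.025^(1/n):
- n = 10: 30.8%
- n = 30 (if escalation ends after three levels): 11.6%
- n = 60: 6.0%

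**5. Effect of a common background on dose comparisons**
Let b be the proportion of patients with a probe or surgical event, equal at all doses, with at most one event per patient. In the difference between two levels b cancels on average, so it creates no systematic trend. It does add noise. The standard deviation of the difference in counts from background alone is √(2 × 10 × b × (1 − b)):
- b = 5%: √0.95 = 0.97 events
- b = 10%: √1.80 = 1.34 events
- b = 20%: √3.20 = 1.79 events

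As shares of a 10-patient level these are about 10, 13 and 18 percentage points. The values of b are assumptions, since the article gives none.

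**The case against.** The case against is substantial, and much of it stands.

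- A reader might infer that expedited reporting covers ICG events only. It does not. The significant-event list is expressly open, it includes any event that discontinues the intervention, and serious-event reporting is product-neutral.
- A reader might infer that the equipment condition in 3.12 has no data to trigger it. Serious events, discontinuation events and routine records all reach the investigator, and the condition is not limited to in-trial reports. What is missing is narrower: a named expedited route for non-serious probe events.
- A reader might infer that ICG harm cannot halt the trial. Conditions 1 to 3 of section 3.12 are general and can reach it.
- A reader might infer that probe and ICG harm cannot be told apart. Before surgery they can, and event name and onset date help afterwards.
- A reader might picture a related-event rate at some dose inflated by probe injuries. Section 3.8 plans no table restricted to related events, so the distortion concerns all-event counts.
- Section 3.8 also says data are summarized overall as well as by dose. An overall count, however, still does not identify probe events.
- The field list in 3.10 is open, section 3.15 refers to a guide for completing case report forms, and an article condenses. Finer causality fields may exist there. But the related/unrelated item to the study is stated in the text, not omitted from it, and can be judged as written.

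**Conclusion.** The point holds in a limited form. As written, the causality item does not separate ICG, probe and operation for intraoperative and postoperative events, and the stated presentation is by ICG dose. Any dose-related ICG effect is therefore mixed with a background present at every dose, and the low-risk premise for thoracic probe use has no dedicated summary. The ICG examples in 3.10 and the equipment condition in 3.12 each name one of the two products.

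On size: one event shifts a dose level by 10 percentage points, and an assumed background of 5% to 20% alone gives a between-level standard deviation of about 10 to 18 points. Zero probe events in a level excludes only rates above 30.8%; zero in all 60 would exclude rates above 6.0%, provided events are attributed to the probe and all six levels are filled.

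The background calculation assumes equal background at each level. Levels are filled in order from the lowest dose, so this is not guaranteed. The documents do not show that any event would be missed or that the trial could not be halted. This is a worthwhile and inexpensive correction to recording and presentation; it does not invalidate the design.

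**What to change.** - **Section 3.10:** replace the single relationship item with three: to ICG, to the probe and to the operation.
- **Section 3.8:** keep the count of all events per dose, because attribution is a judgement made in an open trial. Add ICG-related events by dose, and probe-related events over all patients (up to 60).
- **Sections 3.10 and 3.12:** reconcile the significant-event wording and the halting conditions so that both name the same study products. This is a matter of consistency only; no clinical stopping threshold is proposed.

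Cost: two extra EDC fields per event, slightly more investigator judgement, possibly a few more expedited reports, and short wording changes in three sections. No change to sample size or procedures is needed. If the case report form already records these relationships separately, only the wording and the added tables are needed.
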